#### Follow-up visits

After the end of the dental treatments, the children will be recalled every 6 months to reinforce the preventive orientations concerning the diet and biofilm control. Furthermore, the participants will be orientated to contact us in case of a new complaint. In this case, the additional treatment will be immediately made and registered.

After 12 and 24 months, the number of dental surfaces with dental treatment will be determined for all participants. For this, two different examiners, blinded in relation to the experimental group of the children, will evaluate the conditions and the need for new operative interventions. They will record the following:dental surfaces requiring operative treatment (evident dentine caries - cavitated or not);restored dental surfaces requiring replacement (large failures, caries around restorations, and the complete loss of the material will be considered);restored dental surfaces requiring repair (small failures); andteeth requiring endodontic treatment or extraction (in both cases, summing five surfaces per tooth).

Children with treatment needs will be treated by one of our dentists. All children will receive hygiene and dietary instructions, and fluoride products will be applied as needed. After 24 months, the ECOHIS will be reapplied for the children.

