## Background

### Background

Visual inspection is a quick and easy method for caries lesions detection in primary teeth [1]. Moreover, the method has presented high specificity [2], and it is the unique method validated to assess caries lesions activity [3, 4]. For those reasons, it is routinely used in daily clinical practice [1].

Nevertheless, the method has not presented high sensitivity in detecting caries lesions, mainly at proximal surfaces [2]. To overcome this limitation of the visual inspection, many clinical guidelines used throughout the world have advised that dentists take two bilateral bitewing radiographs in children to detect missed caries lesions in primary molars [5–7]. The radiographic method is capable of increasing the sensitivity of visual inspection in primary teeth, decreasing the number of false-negative results in occlusal [2] and proximal surfaces [2, 8].

However, the increase in the sensitivity usually occurs with the expense of a higher number of false-positive results. Considering the dental caries, this increase of false positives may not be good for two main reasons:The prevalence of non-evident caries lesions seems to be low in most populations. Thus, there would be a higher number or diagnostic errors using methods with low specificity than with low sensitivity;A false-positive result would lead to an unnecessary operative treatment, whereas a false-negative result could be followed up and detected further with no consequences for the patient.

In addition, performing unnecessary operative treatment seems to be more costly than missing some caries lesions undetected by visual inspection alone [9].

Some studies have observed this trend of an increased number of false-positive results with the radiographic method [10–13]. However, most of these studies considered the criterion validity of the methods; hence, they compared the results of the methods with the results obtained with a reference standard method. This type of research usually obtained the rate or correct diagnosis of the method, but it is not concerned with the benefits for the patients.

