#### Caries detection procedures

The visual inspection will be done according to the International Caries Detection and Assessment System (ICDAS) [18]. The children will be positioned in a dental chair, under illumination, and they will receive prophylaxis using rotating bristle brush and a pumice/water slurry. The examiners will use a dental mirror and a ball-ended probe for the examination. The teeth will be examined wet, and then, they will be air-dried for 5 s with a 3-in-1 syringe. The examiner will also evaluate the caries activity status if a caries lesion is present [19]. The condition and treatment decision of each dental surface will be recorded on an appropriate form.

In all cases, the clinical evaluation will be performed without knowledge of the experimental group of the participant. After the examination, the examiner will be informed of the enrollment group and will plan the treatment with or without access to the bitewing radiographs.

For the children allocated to the experimental group, the same examination procedure will be done, but a visual inspection and radiographic examination will be used to reach the treatment decision. Radiographic evaluation will be performed using a light box.

The treatment plan elaborated according to the allocated group will be put in envelops that will be delivered for the dentists responsible for performing the dental treatment. On the first day of treatment, the children will receive orientation for oral hygiene and dietary advice, and an anamnesis will be performed with the parents of the children. Dentists will perform the dental treatment following the plan and according to the predetermined protocols for each type of treatment.

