#### Dental treatment protocols

The choice of the protocols of treatment is based on the best available evidence:Operatory treatments will be done with partial caries removal [20].High-viscosity glass ionomer cement will be used to restore cavitated active caries lesions in occlusal [21] or approximal [22] surfaces (score 4 of ICDAS or higher and/or lesions reaching the outer half of the dentin in the radiographic image).Resin-modified glass-ionomer cement will be used for restorations of lesions involving more than two surfaces [23].Non-cavitated active caries lesions will be treated with fluoride varnish [24].Prevention measure orientation will be based on the orientation of oral hygiene using fluoride dentifrice with 1000 to 1500 ppm of fluoride [25] and dietary advice [26].Endodontic treatment will use iodoform paste [27, 28].Dental extractions and other types of treatment will be provided.

The dentists responsible for the treatments will not receive the bitewings radiographs of the participants; they will only have access to periapical radiographs that may be useful for indirect pulp capping, endodontic treatment, and extraction.

During the operatory interventions, the presence of soft or hard carious tissue or the absence of carious tissue will be evaluated in order to record possible false-positive diagnosis for dentine caries.

The time required for all procedures and the materials used will be registered by an external examiner for the economic analysis. The time spent for each procedure, including return visits, will be considered in calculations of the direct and indirect costs.

The number of visits of each participant and the procedure done at each session, with their respective duration times, also will be recorded. For the calculation of direct costs, we will consider the average of market prices of the materials used in each procedure [29, 30]. Such values will be obtained by averaging the prices from different sources for the products being used, and these numbers will be updated during the study. For the calculations, indirect costs will be also considered, as described in previous studies [29, 30].

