#### Outcomes

The primary outcome will be the number of dental surfaces with operative treatment needs in the follow-up. This outcome is composed of several mutually exclusive factors: number of surfaces with new dentin caries lesions; number of restored surfaces with necessity of replacement; tooth with pain episode and/or necessity of endodontic treatment and tooth indicated for extraction.

The separate components of the primary outcome will be considered as secondary outcomes. Other secondary outcomes will be the impact of oral health on quality of life, number of false-positive results, number of new lesions in the first permanent molars, cost-efficacy and quality-adjusted life year.

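### Caries at a restored surface is counted as replacement, so the new-caries and replacement components can shift between arms without any difference in later caries; the composite primary outcome is not affected by this

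*Protocol article*

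**What the plan says.** The Follow-up visits section of the protocol article lists what the blinded examiners record at 12 and 24 months. One item is "dental surfaces requiring operative treatment (evident dentine caries - cavitated or not"). A separate item is "restored dental surfaces requiring replacement (large failures, caries around restorations, and the complete loss of the material will be considered"). The second item pools three reasons, one of which is caries.

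The Outcomes section says of the primary outcome: "This outcome is composed of several mutually exclusive factors". It names among them "number of surfaces with new dentin caries lesions; number of restored surfaces with necessity of replacement". It then adds: "The separate components of the primary outcome will be considered as secondary outcomes".

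Three statements elsewhere link restored status to allocation:

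- Caries detection procedures: once told the group, the examiner "will plan the treatment with or without access to the bitewing radiographs".
- Dental treatment protocols: the description of lesions to be restored includes "score 4 of ICDAS or higher and/or lesions reaching the outer half of the dentin in the radiographic image".
- Background: "The radiographic method is capable of increasing the sensitivity of visual inspection in primary teeth". The same section expects false-positive findings to lead to extra operative treatment.

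**The concern.** A lesion found at follow-up on a surface without a restoration is new dentine caries. A lesion found beside a restoration is a replacement. Which label applies depends on whether the surface was restored at entry, and the randomised strategy is expected to change that. Each extra surface restored because of a bitewing leaves the set that can yield new caries and enters the set that can yield a replacement. This includes any sound surface restored on a false-positive finding.

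If bitewings changed nothing about later caries, the radiographic arm would still tend to show fewer new-caries surfaces and more replacements. A reader could take the first as prevention and the second as poorer restorations. The trial is meant to confirm or refute guideline advice on bitewings, so these two secondary results are likely to be read in that way.

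**Working it through.** **The plan's own figure.** The Sample size section gives 103 children per group for the composite (difference 5, SDs 15 and 10, two-sided 5%, power 80%). With z-values 1.960 and 0.842:

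n = (1.960 + 0.842)² × (15² + 10²) / 5² = 7.85 × 325 / 25 ≈ 102.0, or 103 when rounded up to a whole child.

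The figure is reproduced. It concerns the composite only; the protocol gives no planning difference for the separate components.

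**Inputs for the component check**

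- k, the extra surfaces restored per child in the radiographic arm: not in the documents; assumed 1 to 5.
- q, the probability that a surface shows dentine caries at follow-up, set equal in both arms and on restored and unrestored surfaces: not in the documents; assumed 0.10 to 0.44. The top value is 17.6 / 40. The 17.6 new-lesion surfaces over two years come from the Sample size section, which does not say that they are dentine lesions. The 40 is an assumption: eight primary molars, at the five surfaces per tooth used in Follow-up visits.
- f, restoration failure over two years: about 10% (Sample size).

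**Formulas, radiographic arm minus visual arm, per child**

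- New caries: −k × q
- Replacement, relabelling only: +k × q
- Replacement with failure unrelated to caries added: k × [q + f × (1 − q)]. The factor (1 − q) stops a surface with both caries and failure from being counted twice.
- Sum of the two components, which is also the change in the composite: 0 from relabelling; k × f × (1 − q) once failure is added.

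| k | q | New caries | Replacement, relabelling only | Replacement, with f = 0.10 | Composite, with f = 0.10 |
|---|---|---|---|---|---|
| 1 | 0.10 | −0.10 | +0.10 | +0.19 | +0.09 |
| 3 | 0.20 | −0.60 | +0.60 | +0.84 | +0.24 |
| 5 | 0.10 | −0.50 | +0.50 | +0.95 | +0.45 |
| 5 | 0.44 | −2.20 | +2.20 | +2.48 | +0.28 |

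The last column is not relabelling. It is the real consequence of having more restorations that can fail.

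**Counting caries whatever the restored status.** Both arms then have 40 × q carious surfaces, so the difference is 0 in every row.

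**How far the upper end can be trusted.** If the planned 10% failure already includes caries around restorations, replacement would rise by only 0.10 × k, which is 0.1 to 0.5 surfaces. Any larger fall in new caries would then be a real reduction in need. The Background also says that non-evident lesions seem to be uncommon in most populations, which points to a small k.

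**The case against.** The strongest reply is that the rule is the same in both arms and is applied by blinded examiners. Restored status is itself an effect of the strategy, so the per-child count of surfaces needing replacement is a valid randomised estimate of that treatment need. The Outcomes section speaks of operative treatment needs, and the protocol nowhere says that the components will be read as caries incidence or restoration quality. All of this stands. It limits what the counts mean, but does not remove the shift: a common rule and blinding cannot prevent a change of label that follows from what was restored at entry.

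A second reply is that the first follow-up item does not say it is confined to unrestored surfaces. That is correct. The reading is an inference from the wording of the replacement item together with mutual exclusivity. It is the natural reading, because otherwise a carious restored surface would fall under both items.

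A third reply is that the examiners also record surface conditions, so the reason for a replacement may already be on the form. The article does not say so. If it is, the fix is cheaper still.

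A reader might go further and infer that the primary outcome is biased, or that the component comparisons are invalid. The documents support neither. A surface adds the same amount to the composite under either label, and the components are sound as counts of need by type. Nor should the shift be judged against the planned difference of 5 surfaces, which belongs to the composite.

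**Conclusion.** The point holds for two secondary outcomes and for how they can be interpreted. On the protocol's own expectation of more restorations with bitewings, equal later caries would still produce a lower new-caries count and a higher replacement count in the radiographic arm. The shift is k × q per child, about 0.1 to 2.2 surfaces under the assumed ranges. The upper end is unlikely, and no value can be fixed from the documents. The direction rests on more surfaces being restored at entry in the radiographic arm; the size also rests on equal caries risk on restored and unrestored surfaces. This is a cheap improvement to make, not a flaw in the primary comparison.

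**What to change.** Keep the composite as it is. Have the follow-up examiners record which of the three listed reasons (caries around the restoration, large failure, complete loss) led to each replacement. Report as the caries component dentine caries on any primary-molar surface, restored or not. Report replacement without caries separately. Give both per child, by randomised arm.

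Failure per restored surface may be shown beside the number of surfaces restored at entry, but as a descriptive rate only. Its denominator arises after randomisation, and restored sound surfaces could dilute it.

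The cost is one extra form item and reworded component definitions. For 12-month visits already done, the reason must be recovered from records. Sample size, treatment and the primary analysis do not change.

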#### Outcomes

The primary outcome will be the number of dental surfaces with operative treatment needs in the follow-up. This outcome is composed of several mutually exclusive factors: number of surfaces with new dentin caries lesions; number of restored surfaces with necessity of replacement; tooth with pain episode and/or necessity of endodontic treatment and tooth indicated for extraction.

The separate components of the primary outcome will be considered as secondary outcomes. Other secondary outcomes will be the impact of oral health on quality of life, number of false-positive results, number of new lesions in the first permanent molars, cost-efficacy and quality-adjusted life year.

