No study performed to evaluate caries diagnosis strategies has ever evaluated important outcomes for the patients. A correct diagnosis is not necessarily a benefit for the patient. For instance, the detection of a caries lesion in a primary tooth near its exfoliation is not good for the patient because it would lead to unnecessary operative treatment. Therefore, studies that evaluate the benefits for the patients are essential to evaluate the actual utility of radiographic method to detect caries lesions in primary teeth. This reason motivates the realization of the present study.

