#### Participant timeline

Recruitment will take place from April 2014 to December 2015. Each participant will be enrolled in the study for approximately 25 months in total (1-month RCT – diagnosis and treatment, followed by a 24-month observational period). The timeline with details of the data collection schedule are summarized in Fig. 1.

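### The primary outcome leaves out operative treatment done in the initial month, so fewer follow-up needs with radiographs could partly reflect earlier treatment, and no listed outcome gives the net operative burden

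*Protocol article*

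**What the plan says.** Outcomes defines the endpoint: "The primary outcome will be the number of dental surfaces with operative treatment needs in the follow-up". Its components include "number of surfaces with new dentin caries lesions; number of restored surfaces with necessity of replacement", together with teeth that have pain or need endodontic treatment and teeth indicated for extraction. Follow-up visits says that blinded examiners at 12 and 24 months "will evaluate the conditions and the need for new operative interventions", and that a tooth needing endodontic treatment or extraction is scored as five surfaces.

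Participant timeline describes the schedule as "1-month RCT – diagnosis and treatment, followed by a 24-month observational period". Under Interventions, every child has bitewings taken, but they reach the planning examiner only in the radiographic arm. Dental treatment protocols lists "lesions reaching the outer half of the dentin in the radiographic image" among the criteria for restoring a surface.

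Background gives the reason for the trial: "A false-positive result would lead to an unnecessary operative treatment". It adds that "A correct diagnosis is not necessarily a benefit for the patient", with the example of a lesion found in a primary tooth close to exfoliation.

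Three other planned elements bear on baseline treatment:
- False positives are judged from the tissue found during operative procedures and are a secondary outcome.
- Statistical methods plans a multivariate analysis of how the radiographic examination influences the treatment decision.
- The economic analysis covers the initial examination, treatment and re-treatment.

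**The concern.** The intervention works by changing which surfaces are treated in the first month, and the primary outcome starts counting after that. A lesion visible only on the bitewing can be restored at baseline in the radiographic arm and then scores 0. The same lesion in the visual arm can become evident, be recorded as a need at 12 months and score 1. Each child has had one restoration, and only the timing differs. Randomisation and blinded assessment do not remove this, because it comes from the intervention and the counting window.

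A restoration that was never needed also scores 0 unless it fails. A lower follow-up count with radiographs is therefore compatible with more surfaces operated on in total, and the Discussion section says that a favourable result in the experimental group would confirm the benefit of guideline bitewings. The primary result alone could carry that conclusion without showing how much operative work it took.

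**Working it through.** **1. The plan's own figure.** Sample size gives a difference of 5 surfaces, SDs of 15 and 10, two-sided 5% significance and 80% power. The average variance is (15² + 10²)/2 = 162.5 (SD 12.75). Then n = 2 × (1.960 + 0.842)² × 162.5 / 5² = 102.04, rounded up to 103 per group, as stated. The calculation uses follow-up needs only. No baseline operative rate by arm is given anywhere.

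**2. Set-up of the illustration.** The first two quantities are assumptions. The third is the approximate two-year restoration failure in Sample size.
- x = extra surfaces restored at baseline in the radiographic arm
- f = share of those that pre-empt a need that would have been counted by 24 months
- q = 0.10, failure of restorations over two years

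Assume one surface per lesion and per restoration, and ignore later failure of restorations first placed during follow-up in the visual arm.

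- Primary outcome, difference favouring radiographs: x(f − q) = x(f − 0.10)
- Excess operative burden with radiographs, baseline included: x + xq − xf = x(1.10 − f)

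The first is positive once f exceeds 0.10. The second is positive for every f up to 1. At f = 0.10, one extra restoration in ten pre-empts a need, which is nine unnecessary ones per avoided need.

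**3. Numbers for x = 5 (assumed).**

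| f | Primary outcome, favouring radiographs | Excess total burden with radiographs |
|---|---|---|
| 0 | −0.50 | 5.50 |
| 0.25 | 0.75 | 4.25 |
| 0.50 | 2.00 | 3.00 |
| 1.00 | 4.50 | 0.50 |

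On these assumptions, treating earlier would produce the full 5-surface design difference at x = 5/0.90 ≈ 5.6 if f = 1, or x = 5/0.40 = 12.5 if f = 0.5.

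**4. Sensitivity.** If a pre-empted need would have scored s surfaces, the primary outcome breaks even at f = q/s, and the total burden breaks even at f = (1 + q)/s.

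| q | s | Primary outcome favours radiographs above f = | Unnecessary restorations per avoided need at that point | Total burden higher with radiographs below f = |
|---|---|---|---|---|
| 0.10 | 1 | 0.10 | 9 | always (1.10) |
| 0.20 | 1 | 0.20 | 4 | always (1.20) |
| 0.30 | 1 | 0.30 | about 2.3 | always (1.30) |
| 0.10 | 5 | 0.02 | 49 | 0.22 |

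The last row is the extreme case in which every pre-empted lesion would have become a five-surface event. The two measures then disagree only for f between 0.02 and 0.22. Above 0.22, radiographs lower the total burden as well.

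**The case against.** The strongest reply is that the trial does look at overtreatment. The primary outcome counts replacement of failed restorations, false positives are recorded on opening the tooth, costs include the initial treatment, and an analysis of treatment decisions is planned. A reader might infer from the endpoint definition that the trial cannot see overtreatment at all. These elements show that this reading is not supported. They still leave a gap. A true lesion restored needlessly, which is the Background section's own example, contains carious tissue and is not a false positive. Costs measure time and materials, not surfaces. The decision analysis addresses the plan at the start, not the balance at 24 months. Follow-up visits opens with a loose phrase about surfaces with treatment, but its next sentences confine the record to new needs.

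A second reply is that the break-even figure is not a property of the plan. This stands. The 10% is a rate per restoration while the outcome counts surfaces, and a missed lesion that progresses can score five. One in ten should not be read as an estimate of bias.

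A third is that early treatment may be a real benefit, and that asking whether tested children fare better afterwards is a legitimate choice of outcome. This also stands, and is why the primary outcome should be kept. A total count has the opposite lean: under the one-surface assumptions it goes against radiographs even when f = 1.

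Lastly, the tilt runs against the working hypothesis in the abstract, which expects little influence of radiographs. A null or adverse result for radiographs would therefore be no less convincing. The result at risk of being misread is a favourable one.

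**Conclusion.** The point holds in a limited form. The primary outcome omits operative treatment in the month where the arms differ by design, so an advantage for radiographs could partly be a matter of timing and could accompany more surfaces operated on overall. Overtreatment reaches the primary outcome only through later restoration failure. Other planned analyses pick up part of the remainder, but none covers needless restoration of a true lesion, and none sums baseline and follow-up operative surfaces.

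The direction follows from the design. The size is unknown, because neither x nor f can be taken from the document. The threshold of about one in ten rests on one surface per lesion and per restoration and on 10% failure. It rises to 0.20 or 0.30 if failure is 20% or 30%, and falls to 0.02 if every missed lesion would have become a five-surface event. In that last case radiographs can also reduce the total burden. The document does not support reading the primary outcome as invalid or the bias as a known quantity.

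**What to change.** Keep the primary outcome and the sample size. Add to Outcomes a named key secondary outcome: the number of surfaces operatively treated or in need from randomisation to 24 months, baseline plus follow-up, analysed with the same model as the primary outcome. State whether a surface restored and later needing replacement counts once or twice (the arithmetic above counts it twice), and how the five-surface rule applies to baseline endodontic treatment and extraction. Also report baseline operative surfaces by arm. Add a sentence that any claim of benefit from bitewings must be read beside this outcome.

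No new data are needed. Caries detection procedures records the treatment decision for each surface, and Dental treatment protocols already records "The number of visits of each participant and the procedure done at each session". The cost is one more secondary analysis and a short definition. Because the total leans against the arm that treats early, the text should say that it supplements the primary outcome and does not replace it.
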